### 2.3. Recruitment and Randomization

The recruitment of the study participants was carried out by social and healthcare professionals from seven participating healthcare centres: Alfahuir Health Centre, Salvador Pau Health Centre, Benimaclet Health Centre, Serrería I Health Centre, Salvador Pau Allende Health Centre, República Argentina Health Centre, and Chile Health Centre. All of these centres belong to the Malvarosa-Clinic Health Department in the city of Valencia.

The general practitioners, who are familiar with their patient’s clinical record, contacted them to ensure that these individuals met the inclusion criteria mentioned above, ensuring their potential eligibility as participants. Once included, participants were requested to complete the baseline assessment. Following the completion of the baseline questionnaire, the allocation of study participants into either the intervention or control group occurred through a randomization procedure. To ensure the concealment of the randomisation sequence, the Oxford Minimization and Randomization (OxMaR) system was employed. This computer-based centralised method ensures proven security measures to prevent bias in the sequence [32]. For safeguarding personal information, every participant was assigned an identification code that corresponds to their group and the specific healthcare centre with which they are affiliated.

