### 2.4. Data Collection Process

Data collection and measurement were conducted using an assessment questionnaire that included the International Consortium for Health Outcomes Measurement (ICHOMs) [33] dataset for the older population, as well as additional measurement questionnaires. Each instrument comprising the assessment questionnaire is described in the Section 2.7. Measurement instruments without validated translation into Spanish were translated using the back-translation method to ensure cross-cultural adaptation of the measures.

Researchers inputted the paper-based collected data into the Generic Medical Survey Tracker (GemsTracker) software, chosen for its security measures and capability to collect, submit, and make modifications to the data. Data were collected from participants in three phases: at baseline (T0), 12 months after the end of the intervention (T1), and 18 months (T2).

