The initial assessment (T0) included a comprehensive evaluation of the physical and mental health of the total study sample based on the International Consortium for Outcome Measurement (ICHOM) as a standard set for older people. The main outcome was the health-related quality of life score measured through the Patient-Reported Outcomes Measurement Information System—Global Health (PROMIS-10), which is a 10-item survey that assesses physical health, mental health, satisfaction with social activities and relationships, and quality of life [50]. In particular, to evaluate psychosocial frailty, the Tilburg Frailty Indicator (TFI) was used, which is an instrument that includes the physical, psychological, and social dimensions of frailty [33]. Loneliness was assessed with the UCLA 3-item Loneliness Scale [35]. Health-related quality of life was assessed with the EQ-5D-5L [51], and lifestyle was evaluated in terms of the BMI, smoking, alcohol consumption, physical activity, and nutrition. Moreover, falls were assessed using the previous history of falls and the Visual Analogue Scale for Fear of Falling [52]. Medication adherence was assessed with the Medication Risk Questionnaire (MRQ-10) [53]. Healthcare utilization was assessed with the Modified SMRC Health Care Utilization Questionnaire 18 [54], and finally, socio-demographic data (age, sex, educational level, type of household income, net monthly household income, marital status, and household composition) were also collected.

Complementary to the baseline questionnaire, protein intake was assessed using the Proteiner Screen 55+ [55], and physical performance was evaluated in terms of balance, walking speed, and lower limb strength to get up from a chair using the Short Physical Performance Battery (SPPB) [56].

Table 1 describes the outcome measures used in the evaluation for older people.

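### The participant identification code is tied to the allocated arm; its stated privacy purpose does not need this, and it can reveal the arm to staff who could otherwise be kept unaware

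*Protocol article*

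**What the plan says.** Section 2.3 (Recruitment and Randomization) gives the order of events. "Following the completion of the baseline questionnaire, the allocation of study participants into either the intervention or control group occurred through a randomization procedure". The sequence is protected by a central system: "To ensure the concealment of the randomisation sequence, the Oxford Minimization and Randomization (OxMaR) system was employed". The same paragraph then turns to identifiers and gives their purpose: "For safeguarding personal information, every participant was assigned an identification code". On what the code contains, it says that "every participant was assigned an identification code that corresponds to their group and the specific healthcare centre with which they are affiliated". No other purpose is given for it.

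Section 2.4 (Data Collection Process) says: "Researchers inputted the paper-based collected data into the Generic Medical Survey Tracker (GemsTracker) software". It adds that the software was chosen partly because it allows entered data to be changed. It does not say which identifier the paper forms carry.

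Section 2.7 (Outcomes) makes PROMIS-10, a patient-reported survey, the main outcome. It also says that "physical performance was evaluated in terms of balance, walking speed, and lower limb strength", using the SPPB. That battery is introduced as an addition to the baseline questionnaire and is missing from Table 1 (effectiveness outcomes). The Discussion nevertheless counts physical performance among the domains in which benefit will be measured.

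The article does not say that participants, assessors, data-entry staff or analysts are blinded.

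**The concern.** In a trial of monthly motivational meetings against usual care, participants know what they received. What can still be protected is the conduct of people who score, enter, clean or analyse data and have no other reason to know the arm. An identifier that carries the arm works against that protection and brings no stated benefit.

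Knowledge of the arm could influence how a timed or rated performance test is run and scored, how an incomplete or ambiguous paper answer is resolved, which entries are queried or changed, and which choices are made during analysis. Each of these routes can be avoided by the way the code is built. The point concerns a rule that the article states, not a detail that it leaves out.

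**Working it through.** There is no figure to reproduce here. The check is a comparison of the relevant statements.

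**1. Does the code carry the group?** Section 2.3 says that it corresponds to group and centre. The natural reading is that it is built from these two elements. A looser reading is that a separate key links the code to them. That is possible but strained: a key links any identifier to every fact about a participant, so there would be little reason to single out these two.

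**2. Does the stated purpose need this?** No. Pseudonymisation needs a code that does not identify the person. Adding the arm does not make the person harder to identify.

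**3. When can it act?** Allocation follows the baseline questionnaire (Section 2.3), so T0 answers are given before a group exists. Any effect is confined to what happens after randomisation: T1, T2, data handling and analysis.

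**4. Is concealment undermined?** No. Concealment through OxMaR protects the next assignment before it is made. A code that reflects a group already assigned does not disclose the next one.

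**5. Who could learn the arm from the code?**

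| Person or step | Could the code reveal the arm? | What the article supports |
|---|---|---|
| Participant self-reporting PROMIS-10 | Not relevant; the arm is already known | Section 2.7, with the intervention in Section 2.5 |
| Intervention staff | Not relevant; the arm is already known | Section 2.5 |
| Researchers giving feedback to controls | Possibly, but they may know it anyway | Sections 2.6 and 4 |
| Assessor of the SPPB at T1 or T2 | Yes, if the test is repeated and the code is on the form | Listed as a benefit domain in the Discussion; absent from Table 1 |
| Person keying or editing paper data | Yes, if the code is on the form | Section 2.4; the code is not mentioned there |
| Analyst | Yes, if the code is kept in the analysis dataset | Not stated |

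**6. How likely is the condition in the last three rows?** Paper records from three time points must be linked within each person, and this code is the only identifier described. Its presence on forms and in the dataset is therefore the natural inference, but it remains an inference.

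**7. Size.** The article gives nothing from which a bias could be derived. Any numerical value would measure only the assumption behind it, so none is given.

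**The case against.** The strongest reply is that nothing is broken. The article claims concealment of the sequence and no blinding of anyone, so the code contradicts no stated safeguard. Who is masked, and how data are recoded before analysis, are details that a condensed article may leave to the full protocol or the analysis plan. The main outcome is self-reported by people who know their arm, and a neutral code does not change that. Researchers who give feedback to controls may know the arm in any case. The SPPB, the clearest example of a staff-measured outcome, has no firmly fixed role at T1 and T2.

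All of this stands as a limit on the point. A reader might infer that blinding of assessors, data entry and analysts has been lost, or that everyone who handles follow-up material can see the arm. The document supports neither inference. The first presupposes blinding that the article never claims. The second needs three facts it does not give: that the group is legible in the code, that the code is on the T1 and T2 forms, and who has access to it.

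The reply does not remove the core. The rule linking code to group is stated, its stated purpose does not require it, and data-entry staff and analysts need not know the arm. Unavoidable bias in self-report is no reason to accept an avoidable route elsewhere.

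**Conclusion.** The point holds in limited form. The article fixes an identifier that is tied to the arm, without need, and this can unmask data-entry staff, analysts and any follow-up assessors not otherwise aware of the allocation. The conclusion rests on two assumptions: that the group can be read from the code, and that the code appears on follow-up forms or in the dataset. Both are likely, and neither is stated. For assessors, it also depends on the SPPB or another staff-measured outcome being collected at T1 or T2.

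The consequence for the main outcome is probably small, because the dominant source of bias there is the participants' own knowledge of their arm. The size cannot be estimated from the document. This is a cheap improvement to trial conduct. It does not show that the results are biased, and it does not undermine the randomisation.

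**What to change.** Use an arm-neutral identifier, assigned at T0 before allocation; a centre prefix is acceptable. Hold the link between identifier and group only in OxMaR and with the intervention staff. The article reports coding in the past tense, so codes probably exist already. In that case re-key them before any remaining assessments and before data go to the analyst, and release the key after database lock. If follow-up is complete, re-keying can still protect the analysis. It would also help to state which roles are kept unaware of the arm and which cannot be.

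The cost is one re-key table and a small risk of linkage error, which a check of the old code against the new one for every participant would limit. No extra participants or visits are needed. Re-keying will not mask staff who know the arm from giving feedback or delivering the intervention. Masking follow-up assessors would also require that they do not hold those roles, and that may have staffing costs which the re-key table does not cover.

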### 2.4. Data Collection Process

Data collection and measurement were conducted using an assessment questionnaire that included the International Consortium for Health Outcomes Measurement (ICHOMs) [33] dataset for the older population, as well as additional measurement questionnaires. Each instrument comprising the assessment questionnaire is described in the Section 2.7. Measurement instruments without validated translation into Spanish were translated using the back-translation method to ensure cross-cultural adaptation of the measures.

Researchers inputted the paper-based collected data into the Generic Medical Survey Tracker (GemsTracker) software, chosen for its security measures and capability to collect, submit, and make modifications to the data. Data were collected from participants in three phases: at baseline (T0), 12 months after the end of the intervention (T1), and 18 months (T2).

### 2.5. Description of the Intervention: Design and Implementation

An intervention protocol incorporating aspects like motivational interviewing, social prescription, the transtheoretical model, and person-centred care, was formulated based on an extensive literature review. This review aimed to identify evidence-based interventions addressing psychosocial frailty and establish the methodology to be employed in the intervention process. Moreover, this intervention protocol includes the phases and procedures to be followed to guarantee the effectiveness and sustainability of the intervention. Social and healthcare professionals, including psychologists and social workers, collaborated to design and implement the ValueCare intervention in the Valencia pilot, specifically tailored for individuals aged over 65 experiencing frailty.

All individuals (120) within the intervention group identified as experiencing frailty participated in the intervention phase. After completion of the baseline assessment questionnaire (T0) by the intervention participants, their results were extracted to validate the presence of psychosocial frailty according to the Tilburg Frailty Index [34] and the UCLA 3 Items Loneliness Scale [35].

Participants identified as frail commence the intervention phase by engaging in an initial meeting with social and healthcare professionals. This initial meeting serves a dual purpose: firstly, to present and elucidate the results derived from the baseline questionnaire to the participants, and secondly, to collaboratively design a personalised value-based care plan using a consensus-based co-design approach. This plan was crafted based on the results, preferences, and interests of the participants and will undergo periodic reviews as part of a shared decision-making process.

During the 12 months of the intervention, participants engaged in regular meetings (once a month) with the social and healthcare professionals responsible for their follow-up, during which motivational interviews were conducted. The motivational sessions aimed to achieve several objectives: identifying the psychosocial needs of the individual; assessing the person’s stage of change according to the Transtheoretical Model by Prochaska and DiClemente [36]; fostering motivation to steer the individual towards a readiness for change by assisting in exploring and resolving ambivalences about unhealthy behaviours or habits; and ultimately, collaboratively establishing objectives through a professional–patient negotiation process to guide the transition toward desirable behaviours. The motivational interviews allow a space of trust where the professional’s attitude is one of acceptance and empathy towards the patient’s needs, preferences, and experiences in order to increase and strengthen personal motivation and commitment to change, helping the participant to explore and resolve the ambivalence that arises in people when they have to make decisions that involve behavioural change.

At the end of each monthly motivational session, specific psychosocial objectives focusing on enhanced social participation and the expansion of social networks are agreed with the participant. These objectives will be revisited by social and healthcare professionals in the subsequent meeting for review. The objectives are embedded in the framework of the term “social-prescribing”, where the professional, during the motivational interview, presents to the participant the existing community resources that could potentially enhance their health and well-being [37,38]. These resources are tailored to match the participants’ psychosocial needs, interests, and preferences. Among the community resources introduced may be activities promoted by third-sector entities (associations, foundations, community groups, NGOs…), as well as resources provided by municipally owned institutions such as libraries, art museums, sports centres, theatres, retirement centres, and even the use of a municipality’s green spaces [39,40].

Apart from the motivational sessions with social and healthcare professionals, participants are able to engage in social workshops organized on a monthly basis in each of the health centres participating in the study. These workshops offer opportunities for interaction among participants within the intervention group. Additionally, communication will be facilitated through WhatsApp groups and the dedicated ValueCare APP, allowing further interaction and engagement among participants. In this way, face-to-face relationships are strengthened through information and communication technologies, doubly favouring the active participation of older people in the community, reducing social frailty and improving mental well-being [41].

Specifically, the ValueCare application (Vodafone Innovus, Athens, Greece) [42] is a mobile application with which the participants of the intervention group will be able to interact and through which the achievement of the prescribed goals will be encouraged and healthy lifestyles will be promoted. To ensure that the ValueCare digital solution is adapted to the local context as well as to the needs and interests of older people, informal caregivers, managers, policy-makers, ICT experts, and health and social practitioners, strategies based on collaborative approaches such as co-design are implemented. In this sense, co-design is paramount to providing integrated person-centred care, as it allows for the involvement of all stakeholders in the development of digital health solutions [43]. A total of 2 rounds of co-design were implemented before the ValueCare implementation phase with 212 participants. All co-design rounds included focus group sessions to explore the opinions, perceptions, preferences, and experiences of the target groups around the ValueCare concept and ValueCare solution. A more generic first round aims to define the value-based model and the digital solution to build the concept and the digital solution according to the needs of all stakeholders, presenting and discussing the added value of the value-based concept in today’s society. The second, more specific co-design round aims to define the technical features and properties of the ValueCare solution as well as its involvement and interaction during the implementation phase of the intervention.

The ValueCare application provides each participant with the personalised care plan that has been agreed upon during the professional-participant co-design process. Participants can visualise in the application which are the weekly objectives to be met. Healthcare professionals are in charge of sending these objectives and monitoring the progress of the participants through the Vida 24 web platform (Vidavo S.A., Thessaloniki, Greece. Vida 24 [44] consists of a connected care IT platform that has been operational in Europe for over 10 years and which allows data from multiple sources to be synchronised, personalised, and adapted to specific needs, allowing participants to view the information in the ValueCare Application and professionals to view real-time information on the participants in the Vida 24 platform. In addition, the platform will integrate a virtual coach tool developed by the Fondazione Bruno Kessler [45] that will act as a persuasive chat bot based on dialogue to motivate participants to achieve their objectives and reinforce positive behaviours. In addition, the ValueCare application has different sections where participants can view content in video or text format on existing resources at the community level to maintain an active and healthy lifestyle, tips to increase their social participation, and knowledge on physical frailty, social frailty, and loneliness, among others.

### 2.6. Control Group

During the 12-month intervention phase, the control group, comprising 120 individuals, continued to receive their usual care, visiting primary care centres or hospital care centres to receive attention when needed, as they did before their involvement in the project. Upon completion of the intervention phase, control group participants undergo follow-up evaluation and receive a comparative health outcomes report contrasting T0 and T1. Additionally, a comprehensive guide offering advice on physical, psychological, and social health promotion is delivered to these participants. This guide presents the assets/opportunities available in their local area, encouraging physical activity, healthy eating, and enhancing their active participation in society.

Figure 1 details the flow of participants from recruitment to the last follow-up contact for control and intervention subjects.

### 2.7. Outcomes

First, the screening process for participant eligibility involved the assessment of frailty, dependency levels, and cognitive impairments, according to the inclusion and exclusion criteria.

The FRAIL scale [46] was the tool selected to categorise the level of frailty among participants. It is a commonly used tool that presents a simple and quick assessment that helps identify the presence of frailty based on five key components: fatigue, endurance, ambulation, illness, and weight loss. If the older adult scores ≥1, a high likelihood of frailty is considered to exist [47], and then it meets the criteria for inclusion in the study.

The level of dependency was assessed with the Barthel Index [48]. The Barthel Index is an ordinal scale that measures a person’s ability to perform 10 activities of daily living (ADLs) by providing a quantitative estimate of the subject’s ability to carry out these activities. The ADLs included in the index are eating, personal grooming, toileting, bathing/showering, transferring between the chair and bed, transferring (walking on a smooth surface or in a wheelchair), going up/downstairs, dressing/dressing, stool control, and urine control. Participants were excluded from this study if they scored >60 points on this index.

Finally, cognitive impairments were assessed using the SPMSQ [49], which is a short assessment questionnaire with 10 questions that allows the exploration of different cognitive areas, specifically assessing the functions of orientation, recall memory, concentration, and calculation. If the older adult obtains a score between 0 and 2 on this questionnaire, it is considered a highly suggestive result of cognitive impairment, and the participant is excluded from the study.

The initial assessment (T0) included a comprehensive evaluation of the physical and mental health of the total study sample based on the International Consortium for Outcome Measurement (ICHOM) as a standard set for older people. The main outcome was the health-related quality of life score measured through the Patient-Reported Outcomes Measurement Information System—Global Health (PROMIS-10), which is a 10-item survey that assesses physical health, mental health, satisfaction with social activities and relationships, and quality of life [50]. In particular, to evaluate psychosocial frailty, the Tilburg Frailty Indicator (TFI) was used, which is an instrument that includes the physical, psychological, and social dimensions of frailty [33]. Loneliness was assessed with the UCLA 3-item Loneliness Scale [35]. Health-related quality of life was assessed with the EQ-5D-5L [51], and lifestyle was evaluated in terms of the BMI, smoking, alcohol consumption, physical activity, and nutrition. Moreover, falls were assessed using the previous history of falls and the Visual Analogue Scale for Fear of Falling [52]. Medication adherence was assessed with the Medication Risk Questionnaire (MRQ-10) [53]. Healthcare utilization was assessed with the Modified SMRC Health Care Utilization Questionnaire 18 [54], and finally, socio-demographic data (age, sex, educational level, type of household income, net monthly household income, marital status, and household composition) were also collected.

Complementary to the baseline questionnaire, protein intake was assessed using the Proteiner Screen 55+ [55], and physical performance was evaluated in terms of balance, walking speed, and lower limb strength to get up from a chair using the Short Physical Performance Battery (SPPB) [56].

Table 1 describes the outcome measures used in the evaluation for older people.

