### 2.2. Study Participants: Inclusion and Exclusion Criteria

The study sample was composed of 240 older adults experiencing frailty (120 individuals in the intervention group and 120 in the comparison group). Participants were randomly assigned to each of the groups. Expecting a 20% loss to follow-up between T0 and T1 (e.g., due to mortality, rehousing, or study withdrawal), we expected to obtain complete data from 96 participants in the intervention group and 96 participants in the control group of each large-scale pilot site (in *n* = 192 study participants with complete data at follow up, equally divided over the intervention group and the control group). We assumed equal standard deviations in the intervention group and the control group, an alpha level of 0.05, and a power of 0.80. For this expected overall sample size and assumptions, with regard to the continuous outcome measures, a difference of 0.23 SD (standard deviation) between the intervention group and the control group can be detected at follow-up.

Participants in the intervention group engaged in a 12-month intervention phase tailored to their needs, receiving a personalised care plan agreed through a shared decision-making process, whereas those in the comparison group maintained their usual care. All participants were evaluated at baseline, after 12 months, and after 18 months.

The inclusion criteria encompassed individuals aged 65 or above, experiencing frailty, residing independently within the community, and affiliated with one of the seven healthcare centres under the Malvarrosa-Clinic Health Department within the Valencia study area. The exclusion criteria involved individuals with cognitive impairments, significant dependency, institutionalisation, inability to provide informed consent, or lack of proficiency in the Spanish language.

Patients who met the inclusion criteria were invited to participate in the ValueCare project, where a comprehensive explanation of their involvement in the project was provided. Patients interested in participating in this study were requested to sign the informed consent form, indicating their voluntary, informed, and explicit consent to participate in this study and permit the processing of their data.

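### The Barthel exclusion points the wrong way: as written, it removes the more able people the trial is meant to recruit and keeps the more dependent ones

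*Protocol article*

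**What the plan says.** Section 2.2 of the protocol article sets the population in words. It includes "individuals aged 65 or above, experiencing frailty, residing independently within the community", and among those it excludes are "individuals with cognitive impairments, significant dependency, institutionalisation".

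Section 2.7 turns these criteria into screening tools and says that the screening followed the inclusion and exclusion criteria. For dependency the tool is named: "The level of dependency was assessed with the Barthel Index". The index is described as "providing a quantitative estimate of the subject’s ability to carry out these activities". The paragraph ends with the rule: "Participants were excluded from this study if they scored >60 points on this index".

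Table 1 also lists activities of daily living as an effectiveness outcome, measured with a modified 10-item Barthel Index.

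**The concern.** A score that estimates ability rises with ability. Excluding scores above 60 therefore excludes the able end of the scale, although the criterion being applied is meant to exclude the dependent end.

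This is the only numerical threshold the article gives for that criterion. If the centres followed it literally, the Barthel step would pass only people with low ability in daily living. The intervention in section 2.5 relies on monthly workshops at the health centres and on community resources such as libraries, museums and sports centres. One would expect such people to find these hardest to use, though the article has no data on this. The results would then describe a different population from the one in section 2.2.

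There is a secondary effect on measurement. If the Table 1 instrument is scored in the same way as the screening index, the literal rule would cap the baseline value of a listed outcome at 60.

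Even if the rule was never applied this way, anyone who replicates or appraises the trial from the article would work from an inverted criterion.

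**Working it through.** The plan has no figure to reproduce here. The check is one of direction, followed by a listing of what the rule does.

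**Inputs from the article**

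| Item | Content | Place |
|---|---|---|
| Target population | 65 or older, frail, living independently | Section 2.2 |
| Criterion to be applied | Significant dependency is an exclusion | Section 2.2 |
| Tool for that criterion | Barthel Index | Section 2.7 |
| What the score measures | Ability in 10 activities of daily living | Section 2.7 |
| Rule | Excluded if score > 60 | Section 2.7 |

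**Step 1: direction of the scale.** The article does not say in so many words that a higher score means more independence. It does describe the index as "providing a quantitative estimate of the subject’s ability to carry out these activities". A quantitative estimate of ability increases with ability, and nothing in the article says that the scoring is reversed.

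**Step 2: direction of the rule.** Score > 60 leads to exclusion, so the more able are excluded. Score ≤ 60 leads to no exclusion on this tool, so the less able pass.

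**Step 3: comparison with section 2.2.** The criterion there excludes the dependent and seeks the independent. The rule does the reverse.

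**Step 4: listing on an assumed scale.** The article gives no score range. Assume 0 to 100 in steps of 5, higher meaning more able (21 possible values):

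- excluded by > 60: 65, 70, 75, 80, 85, 90, 95, 100 (8 values, including full independence);
- not excluded: 0, 5, …, 55, 60 (13 values, including complete dependence).

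The direction of the contradiction does not depend on this range. It needs only that more points mean more ability.

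**Step 5: overlap with the intended rule.** Suppose 60 is the intended cut and only the inequality is reversed.

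- If the intended exclusion is score < 60, the intended eligible set is score ≥ 60. Its overlap with the literal set (score ≤ 60) is the single value 60.
- If the intended exclusion is score ≤ 60, the intended eligible set is score > 60 and the overlap is empty.

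**Step 6: illustrative size.** Let *p* be the share of otherwise eligible patients who score above 60. The literal rule rejects a share *p* of them and passes 1 − *p*. The article gives no value for *p*. On an assumed range of 0.80 to 0.95, it rejects 80–95% and passes 20% down to 5%. This range is an assumption, and the conclusion does not depend on it.

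**The case against.** The strongest reply is that this is a slip in reporting, not a fault in the trial. Section 2.2 still excludes significant dependency and institutionalisation in words, and still requires independent living. Under section 2.3, general practitioners who knew the clinical records checked the inclusion criteria, so the Barthel cut-off was not the only gate. Someone the Barthel rule fails to exclude is not thereby admitted. Read together, the sections conflict; they do not show that a dependent sample was enrolled.

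Much of this stands. The article cannot show what the screening form said, so the consequences for the enrolled population are conditional on literal use. It also defines significant dependency in no other way, so it cannot be shown that everyone at 60 or below was meant to be excluded. The direction of the scale is inferred from the description, and Table 1 names a modified version of the index without saying whether it is scored in the same way. That makes the point about the outcome scale secondary. The 80–95% range has no source in the article.

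None of this rescues the sentence. The article states a specific numerical rule that says the opposite of the criterion it applies, and no reading of the rest of the text reconciles the two. Nor is this detail that an article may leave to a fuller document: the rule is present, and it is wrong as written.

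**Conclusion.** The concern holds. The Barthel exclusion in section 2.7 contradicts section 2.2 and inverts eligibility on this criterion. The finding rests on one inference, that a score described as an estimate of ability rises with ability. It does not depend on the score range or on any assumed distribution of scores.

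What remains unknown is whether the error is confined to the article or was also on the form used at the centres. In the first case the published criterion is wrong but the sample is unaffected. In the second, the Barthel step selected the opposite of the intended population. Because the sentence is an eligibility rule and the two possibilities differ so much in consequence, it must be corrected and the rule actually used must be confirmed.

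**What to change.** 1. Establish first which rule was applied, from the screening form and the screening records of the seven centres. Rewriting the text before this check could misreport what was done.
2. Reconcile sections 2.2 and 2.7. If the form excluded the low-ability end, reverse the inequality in section 2.7 so that it agrees with section 2.2. State which side a score of exactly 60 falls on, and give the score range and direction of the index. If the literal rule was used, say so and describe the enrolled population accordingly.
3. Report how many randomised participants fail the intended criterion, by arm.
4. State whether the screening index and the modified index in Table 1 are scored in the same way.

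If the error is only in the article, the cost is a one-character correction, a few added words and a check of records already held. If the rule was applied as written, correcting the text is not enough: the article's description of the population, and to whom the results apply, would have to change.
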